### Description of the Intervention

#### Overview

The Healthcare CEO app was developed guided by the user-centered information systems research framework and comprised 3 key cycles: Relevance, Rigor, and Design [41]. It was named after the self-expectations of patients in diabetes management, as patients with T1D often wished to become the “Chief Executive Officers” of their disease. The development and testing process of the Healthcare CEO app is detailed in published articles [42]. The app content was designed based on the results of previous qualitative and Delphi studies [5,23] and consisted of 11 interfaces (as shown in Figure 2): CEO’s Profile; Health Tracking; CEO Knowledge Base; Barrier-free Communication; See Here: Diet and Exercise; Help Me, Detective!; CEO Chat Room; CEO’s Secretary; Who’s the Best CEO; SOS Calls; and Q&A. The evidence-based content aims to enhance disease knowledge among individuals in the transitional phase, improve self-care behaviors, and bolster confidence in disease self-management. These were combined with interpersonal communication skills training, to alleviate disease-related emotional distress, ultimately improving disease control outcomes and QoL. The content, objectives, and expected outcomes of each interface are detailed in Table 1.

**Figure 2 figure2:**
[figure not shown]
Interfaces of the Healthcare CEO app. CEO: chief executive officer.

**Table 1 table1:** Content of Healthcare CEO app.

Interface	Description of content	Purposes and expected outcomes
CEO’s Profile	Personal and disease data, including the following: name, nickname, date of birth, occupation, duration of disease, hospital, and attending physician. The patient can select the data to be openly displayed.	Establish basic data Review and confirm basic disease information through data entry
Health Tracking	Upload or enter data on blood glucose level, blood pressure, body weight, and insulin dosage. HbA_1c_^a^ targets can be set, and changes in HbA_1c_ can be analyzed and displayed as trends.	The status of HbA_1c_ control can be checked to enhance self-care motivation and confidence in disease self-management
CEO Knowledge Base	Basic and advanced knowledge of interest to patients with T1D^b^ in the transition phase is provided in the e-book format. Examples of basic knowledge include the following: impact of secondary sex characteristic development on blood glucose; blood glucose control targets in T1D; and tips for dieting, exercise, and travel during puberty. Examples of advanced knowledge are as follows: matters related to sex, genetics, gestation, and employment among patients with T1D. Both a pretest and posttest must be completed to determine the learning effectiveness of each article before the next article can be accessed.	Patients can enhance T1D-related knowledge on a need basis Patients can boost their confidence in disease management by accumulating disease-related knowledge. This will enhance self-care behaviors, disease control outcomes, and disease-related QoLc
Barrier-free Communication	Guidance for techniques in parent-child, peer, and workplace interactions is provided through video and e-book links. Questions and scenarios are designed to prompt patients to reflect on their communication methods and think about/enact their strategies for effective interaction.	Improve communication skills, enhance ability to deal with interpersonal difficulties, and reduce emotional distress
See Here: Diet and Exercise	Carbohydrate and calorie calculators and a food swap guide are provided. The calorie contents of preferred foods and calories burned in preferred exercises of patients in the transition phase are displayed in images. Patients can keep records using the handy checkbox interface or uploading photos.	Assist in disease management and self-care, which will in turn improve disease control outcomes and disease-related QoL
Help Me, Detective!	When the blood glucose level is not within the expected range or emergency complications occur, this interface allows for the recording of the time of event occurrence, uploading of blood glucose readings, photographs of the patient’s diet, exercise, or patient condition during the event, and documentation of the treatment measures adopted. These data can serve as a reference for discussion with the physician during outpatient visits, and physician advice can be input into the interface to guide the handling of future emergencies.	By recording and analyzing the causes of acute complications, the patient may devise improvement measures to enhance disease control, which will gradually enhance confidence in disease self-management and improve disease control outcomes
CEO Chat Room	An optional second password can be set to achieve 2 levels of privacy protection, which may be very important to patients in the transition phase. Two chat rooms named the “insider chat room” and “outsider chat room” have been designed. The insider chat room is reserved for patients using the app, with 2 themed chats organized monthly. Patients may invite individuals whom they trust (eg, attending physicians, close friends, or primary caregivers) and can engage in heart-to-heart talk using the outsider chat room, to develop their interpersonal networks and exchange views and ideas.	Provide interpersonal support and enhance disease-related knowledge and management strategies through experience sharing, which will alleviate emotional distress and strengthen disease self-management ability
CEO’s Secretary	This consists of 2 functions, namely “Reminders” and “Online consultations.” (1) Reminders: When trends of exceedances related to blood glucose occur, such as excessively high postdinner blood glucose level for 3 consecutive days, noninput of health data for ≥3 days, fewer blood glucose measurements than the required number of measurements for 3 days, and on the day before a scheduled outpatient visit, patients and app administrators will receive notifications and text message reminding them to perform relevant tracking actions. Reminders can also be set based on the needs of the patients; (2) Online consultations: The timing and theme of online consultation sessions can be booked in advance. Online consultations involve the clarification of doubts related to disease care through interactions with health care professionals.	Assist in disease management and provide individualized knowledge to enhance disease-related knowledge and confidence in self-care, thereby alleviating emotional distress and improving disease-related QoL Conditions for reminders can be set to reduce annoying reminders, to prevent resentment of app use
Who’s the Best CEO	One point is awarded every time the user performs data input on time, reads an article, devises a communication technique, and correctly enters data into the Help Me, Detective! interface, or enquires about online consultation. Ten points are awarded when the target HbA_1c_ level is reached. The patients with the highest number of points are listed weekly. At the end of each month in our study, the top 3 patients with the highest number of points will each receive an NT $300 (approximately US $9.24) voucher. Moreover, at the end of the study, the top 3 patients with the highest number of points will receive an NT $1000 (approximately US $30.79) voucher.	Enhance motivation and effort in self-care
SOS calls	Patients can set up 3 contact numbers to call for help quickly when necessary.	Assist in disease management and self-care, thereby improving disease control outcomes
Q&A	Patients who may be unaccustomed to asking questions in the chat room can have their queries answered via the provided email account.	Assist in disease management and self-care to improve outcomes

^a^HbA_1c_: hemoglobin A_1c_.

^b^T1D: type 1 diabetes.

^c^QoL: quality of life.

#### Experimental App Intervention

The complete Healthcare CEO app will be used to intervene in the experimental group. Two trained research assistants will supervise each other to guide the participants in the following aspects, according to the standard treatment manual: (1) account setup; (2) viewing of operation guidance videos; (3) demonstration of all app functions, getting participants to perform app operations, and clarifying doubts about app usage; (4) explaining troubleshooting methods; (5) providing contact information of app administrators; and (6) setting a HbA_1c_ control target. Between every 2 rounds of data collection, the research assistants will contact the participants to check if they have encountered issues or difficulties when using the app, although they will not exchange disease care-related information. After the completion of data collection, the app will be remotely uninstalled by the administrators at the backend.

#### Control App Intervention

Participants in the control group will only install the “CEO’s Profile” and “Health Tracking” interfaces of the Healthcare CEO app. In addition to explanations for the account setup and the use of the 2 interfaces, the research assistants will not provide any app-related information to the control participants. The status and difficulties of app use will also not be tracked. After the last round of data collection, the full version of the Healthcare CEO app will be provided to the control group participants, according to their preferences. The app will be remotely uninstalled at the backend by the administrators after 9 months.

### Measures

#### Overview

All survey questionnaires will be accessed via QR codes and answered online, with all fields set as mandatory to prevent nonresponses. The tools to be used in this study are as follows.

#### Demographic Questionnaire

This self-designed questionnaire has been developed based on the conceptual framework of this study. It includes questions on age, sex, BMI, educational level, occupation, number of hospital stays, complications, age at diagnosis, duration of diabetes, frequency of blood glucose self-monitoring, department responsible for follow-up, number of physician changes, and number of department changes.

#### Primary Outcomes

These include HbA_1c_ levels, percentage with HbA_1c_ <7.0%, and the number of hyperglycemic and hypoglycemic events.

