#### Sample Size

The required sample size was estimated using the G*Power program (Heinrich-Heine-Universität Düsseldorf) for repeated measures with 2 groups, 9 measured variables, power of 0.80, α set at .05, an estimated Cohen effect size of 0.25, and a correlation coefficient of 0.5. The sample size for each group was calculated as 36. By allowing for a potential 25% dropout rate, as suggested by Goyal et al [31], a final sample size of 96 participants (48 participants in each group) was established.

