### Data Collection

Three research assistants with a background in health care, who have a basic understanding of T1D, have undergone training, and are not involved in the provision of health care, will be responsible for the data collection. Attending physicians of patients with T1D will provide referrals of patients who meet the inclusion criteria. One research assistant in charge of data collection will then approach the patients to explain the purposes of the study and the research process. Patients who agree to participate will subsequently fill out the informed consent sheet and undergo the preintervention test (T0) in an undisturbed environment. The second research assistant will obtain the randomization results from the statistician by phone and assist participants in downloading the Healthcare CEO app onto their smartphones based on their group assignment. The third research assistant will check and remind the second research assistant of the intervention steps to ensure the accuracy and completeness of the intervention. Considering that HbA_1c_, the critical indicator of blood glucose control, is measured once every 3 months, the time points for the postintervention data collection for both groups are set at 3 months (T1), 6 months (T2), and 9 months (T3) after the intervention.

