### Data Analysis

#### Statistical Analysis

The intention-to-treat principle will be used for the data analysis; that is, all participants will be included in their initially assigned groups for analysis, regardless of whether they withdraw from the study for any reason or are lost to follow-up. Data will be analyzed using IBM SPSS 26.0 for Windows, with differences considered statistically significant at *P*<.05. Demographic and disease status data, including age, gender, BMI, age at diagnosis, disease duration, and HbA_1c_, along with metrics on the app usage to evaluate treatment fidelity, such as the log-ins to the app, frequency of use for each interface, number of e-books read in the CEO Knowledge Base, and number of online consultations in CEO’s Secretary, will be presented through descriptive statistics. This will include frequency distributions, percentages, means, SDs, and maximum and minimum scores. Homogeneity in the essential attributes of the 2 groups will be compared and analyzed using inferential statistics, such as the chi-square test and ANOVA. Owing to the longitudinal nature of this study, repeated data measurements will be taken. Dependencies may exist among the data at different time points, and data loss may also occur. Using generalized estimating equation models, repeated measurements can be simultaneously included in the regression analysis. Through the variance correction process, consistent estimates of the regression parameters and their variance can be provided to correct for dependencies, and participants with missing values can still be included in the analysis [52]. Therefore, a generalized estimating equation will be used for data analysis to compare the differences between the experimental and control groups at both preintervention and postintervention time points, as well as the differences in the scores of the experimental group before and after intervention.

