### Validity and Reliability

The study design and participant enrollment process were formulated in accordance with the recommendations of the CONSORT (Consolidated Standards of Reporting Trials) statement. We also formulated strategies based on the National Institution of Health Behavior Change Consortium guidelines to monitor the faithfulness and fidelity of the intervention process. The research tools used in this study also exhibit good validity and reliability. In the measurement of the primary outcome variables, this study differs from previous works on diabetes management apps in that “% with HbA_1c_ <7.0%” data will be calculated for the first time for analysis. This allows for greater objectivity and rigor in evaluating the effectiveness of the Healthcare CEO app.

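### Four unranked primary outcomes, compared at three follow-up visits at P<.05 with no lead outcome, lead visit or success rule, leave the error rate of the main claim uncontrolled

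*Protocol article*

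**What the plan says.** - **Outcomes.** Primary Outcomes lists the HbA1c level, the percentage below 7.0% "and the number of hyperglycemic and hypoglycemic events". None is ranked above the others. Validity and Reliability keeps the plural: "In the measurement of the primary outcome variables". Data Collection calls HbA1c the critical indicator of glucose control, but only to explain the spacing of visits.
- **Visits.** Data Collection says that the follow-up assessments "are set at 3 months (T1), 6 months (T2), and 9 months (T3) after the intervention". The Abstract lists group comparisons at baseline and at each of these visits.
- **Analysis.** Statistical Analysis uses generalized estimating equations "to compare the differences between the experimental and control groups at both preintervention and postintervention time points", "with differences considered statistically significant at *P*<.05". It gives no lead visit, testing order, split of alpha or rule for a mixed result.
- **Sample size.** Sample Size assumes 2 groups, 9 measured variables, power 0.80, alpha .05, "an estimated Cohen effect size of 0.25" and correlation 0.5. It arrives at 36 per group, raised to 48 for 25% dropout. It ties none of this to a named outcome.

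**The concern.** The aim is to judge whether the app is effective, and the protocol gives several equally ranked routes to a yes. A significant difference on any of the four outcomes, at any follow-up visit, could be reported as a positive primary result. The stated alpha of .05 then describes each test and not the overall claim. The stated power of 0.80 belongs to no identified test. Nor does the protocol say how to read a split result, such as a gain on one primary outcome and a loss on another.

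Timing adds weight. Results and the Abstract describe a halt after 38 participants, a preliminary report planned for November 2024, and recruitment that resumed in August 2023 with final findings expected by July 2025. A lead outcome chosen late could be chosen with preliminary results in view.

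**Working it through.** **1. The protocol's own figure.** For a between-groups repeated-measures F test, the noncentrality is λ = f²·N·m / (1 + (m − 1)ρ). With f = 0.25, N = 72, m = 9 and ρ = 0.5:

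λ = 0.0625 × 72 × 9 / (1 + 8 × 0.5) = 40.5 / 5 = 8.1.

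On 1 and 70 degrees of freedom this gives power 0.801, and 72 is the smallest even total that reaches 0.80. Then 72 / 0.75 = 96. The stated numbers reproduce, but only with the 9 measured variables entered as nine repeated measurements. With m = 4, the number of time points, power at 72 is 0.754. The calculation has a single alpha of .05 and no named outcome.

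**2. Chance of at least one false difference, one visit.** For four independent tests, 1 − 0.95⁴ = 18.5%. The documents give no correlation between outcomes, so a range is assumed. The remaining rates come from simulated multivariate normal test statistics, counting |z| > 1.96, with equal correlation between outcomes crossed with equal correlation between visits. The .05 is taken as two-sided.

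**3. All three visits.** If each outcome is tested at each visit, there are 4 × 3 = 12 tests. The between-visit correlation is assumed to be 0.5, borrowed from Sample Size.

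| Outcome correlation (assumed) | One visit, 4 tests | Three visits, 12 tests |
|---|---|---|
| 0 | 18.5% | 41% |
| 0.3 | 17.4% | 39% |
| 0.5 | 15.6% | 36% |
| 0.8 | 11% | 27% |

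For outcome correlations from 0.5 to 0, the 12-test figure is 38 to 44% at a visit correlation of 0.3 and 32 to 37% at 0.7.

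**4. Fewer tests.** The section on the HbA1c <7.0% outcome defines a percentage of readings for each participant. That may be one summary per person and not a value per visit. There are then 3 × 3 + 1 = 10 tests, and the rate is about 32 to 36% (outcome correlation 0.5 to 0, visit correlation 0.5).

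**5. Only false results that favour the app.** Counting one direction, with outcomes oriented so that benefit is positive, the rates are 7.8 to 9.7% at one visit and 18 to 23% over three visits. A single two-sided .05 test gives 2.5%.

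**6. Power for a single named contrast.** With two groups, d = 2f = 0.5. With 36 evaluable per group, the noncentrality is d·√(36/2) / √v = 2.121 / √v, where v is the variance of the contrast relative to one measurement. The correlation is 0.5 between any two of T0 to T3.

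| HbA1c contrast | v | Noncentrality | Power |
|---|---|---|---|
| 9 months, unadjusted | 1 | 2.12 | 0.55 |
| 9 months, baseline-adjusted | 1 − 0.5² = 0.75 | 2.45 | 0.68 |
| Mean of T1–T3, unadjusted | (1 + 2 × 0.5)/3 = 0.667 | 2.60 | 0.73 |
| Mean of T1–T3, baseline-adjusted | 0.667 − 0.5² = 0.417 | 3.29 | 0.90 |

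**The case against.** The strongest reply is that this is a condensed article and its analysis plan is not shown. Adjustment of alpha, testing order and exact model contrasts commonly sit in that plan, and a general P<.05 sentence does not rule them out. This stands for the mechanics of adjustment. It does not answer the central point: choosing the primary outcome is the protocol's job, and this protocol chose four of equal rank and set the threshold. A later plan would have to alter that choice, not merely fill it in.

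Other objections limit the size of the point, and they stand:

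- A reader might infer a 36 to 41% chance of falsely declaring the app effective. The documents do not support that. Those rates count false differences in either direction; the favourable ones are about half.
- The ranges rest on assumed correlations. HbA1c and the percentage below 7.0% come from the same readings, so a higher correlation is plausible for that pair and would lower the rates.
- Twelve tests is a reading of the text. Statistical Analysis does not say whether the model yields visit-wise tests, a joint group-by-time test or an averaged effect.
- A reader might take the power calculation to cover one primary outcome. It names none.
- A reader might suppose that naming a single endpoint never costs power. That fails for three of the four contrasts in step 6.

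**Conclusion.** The point holds in this form: the protocol fixes four equal primary outcomes and one unadjusted threshold over three follow-up visits, with no rule for success. Followed as written, it does not hold the error rate of the main claim at .05.

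If any significant primary result counts as success, the two-sided inflation is roughly threefold to fourfold at one visit (16 to 18.5% against 5%). It is about sevenfold to eightfold with visit-wise testing (36 to 41%). The favourable-direction rates of 8 to 10% and 18 to 23% are the fairer measure of a false claim of benefit. Even at an outcome correlation of 0.8, the two-sided rates stay at 11% and 27%. The direction of the problem is therefore firm, while its exact size depends on correlations and contrasts that the protocol does not state.

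**What to change.** 1. Name one primary endpoint and contrast. The preferred choice is the between-group difference in HbA1c, adjusted for baseline and averaged over T1 to T3, tested at two-sided .05.
2. Make the other three outcomes and the individual visits secondary, tested in a fixed order or with Holm. Splitting alpha across the four outcomes without naming a visit is not enough: .0125 each gives 4.7% at one visit but 12.2% over three (outcome correlation 0.3, visit correlation 0.5).
3. Restate Sample Size for the chosen contrast, with its own power.
4. Record that the choice was made without reference to the preliminary results from the first 38 participants.

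**Cost.** The edits are to the outcome, analysis and sample-size text, plus the record in item 4. The other three outcomes can no longer carry the main claim alone. Of the four contrasts examined, only the baseline-adjusted mean reaches the stated 0.80 with 36 evaluable per group, and this assumes d = 0.5 and correlation 0.5. A 9-month contrast would need a larger sample or an openly lower power.

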##### HbA1c

HbA_1c_ will be recorded as a percentage; data will be obtained through venous blood analysis.

##### Percentage With HbA1c <7.0%

The percentage of HbA_1c_ readings below 7.0% for each participant will be calculated.

##### Hyperglycemic Events

The number of events with blood glucose >200 mg/dL or “high” on the glucometer or diagnosed ketoacidosis will be calculated for each participant.

##### Hypoglycemic Events

The number of events with blood glucose <60 mg/dL or “low” on glucometer or diagnosed hypoglycemia will be calculated for each participant.

For hyperglycemic and hypoglycemic events, during the data collection period, the blood glucose readings will be downloaded from the blood glucose meters of the participants, and the number of hyperglycemic and hypoglycemic events will be calculated. Considering that changes in blood glucose levels may be tracked only after adopting treatment measures, 2 researchers will perform a manual inspection of the data simultaneously. Only the first recorded reading, among all readings taken within the same measurement period, will be analyzed.

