#### Knowledge Gaps

Currently, the available apps for diabetes management can be broadly classified into 5 categories: nutrition, physical activity, blood glucose monitoring, insulin titration, and insulin injection. Most apps merely possess a single function, although there is an increasing trend toward integration [37]. Additionally, the majority of Chinese-language apps provide general diabetes knowledge, which may not be applicable to adolescents or young adults, and do not cater to the specific needs of patients with T1D in the transition phase [5]. Furthermore, the effectiveness of such apps should be validated by long-term empirical evidence [24,38], and few studies have mentioned the adoption of strategies to enhance treatment fidelity [31,35]. Health apps developed for intervention should incorporate evidence-based content while fulfilling the needs and protecting the privacy of the target age groups to enhance effective disease self-management [39]. To address the specific needs of patients in the transition phase, we developed the Healthcare CEO app using a user-centered approach. This app targets challenges such as poor glycemic control; pressures related to self-care; effective disease self-management; and interpersonal issues, including the establishment of romantic relationships, concerns about the health and heredity of future generations, workplace adaptation, parent-child conflicts, and enhancing QoL. This study aims to present a comprehensive protocol for evaluating the efficacy of the Healthcare CEO app. This will involve a series of detailed analyses, including (1) comparing disease control outcomes, confidence in self-management, self-care behaviors, emotional distress, and QoL between the experimental and control groups, and (2) a comparison of differences in preintervention and postintervention disease control outcomes, confidence in self-management, self-care behaviors, emotional distress, and QoL in the experimental group.

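### The two glucose-event primary outcomes are raw counts with no stated observation window or denominator at any visit, so their before/after comparison cannot be interpreted

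*Protocol article*

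**What the plan says.** The Primary Outcomes section of the protocol article lists four items: "These include HbA_1c_ levels, percentage with HbA_1c_ <7.0%, and the number of hyperglycemic and hypoglycemic events". Both event outcomes are then defined as plain totals. Under Hyperglycemic Events: "The number of events with blood glucose >200 mg/dL or “high” on the glucometer or diagnosed ketoacidosis will be calculated for each participant". Under Hypoglycemic Events: "The number of events with blood glucose <60 mg/dL or “low” on glucometer or diagnosed hypoglycemia will be calculated for each participant".

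The only timing statement for these totals is in the Hypoglycemic Events section: "For hyperglycemic and hypoglycemic events, during the data collection period, the blood glucose readings will be downloaded from the blood glucose meters of the participants". The same section adds that two researchers inspect the data and that only the first reading within a measurement period counts. That rule removes repeat readings. It does not say how far back the count reaches.

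On timing of visits, the Data Collection section places T0 at enrolment: "Patients who agree to participate will subsequently fill out the informed consent sheet and undergo the preintervention test (T0) in an undisturbed environment". The randomization result and the app download follow. The later rounds are at 3, 6 and 9 months.

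On use of the counts, one of the two aims at the end of Knowledge Gaps is "a comparison of differences in preintervention and postintervention disease control outcomes" in the experimental group. The Statistical Analysis section assigns this to the generalized estimating equation (GEE), which covers the between-group comparison "as well as the differences in the scores of the experimental group before and after intervention".

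**The concern.** An event count grows with the time over which it is collected. Two counts from the same patient can be compared only if they cover the same length of time, or if each is divided by the time it covers. The article does neither.

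T0 is the visit most exposed. There is no run-in and no prospective baseline period, and patients are referred by their attending physicians from clinic or ward. The T0 count can therefore come only from history already stored in the meter, and its length may differ from patient to patient. Later visits at least have a natural interval since the previous round, although the article does not say that this interval is the window.

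Two things are at stake. First, the before/after comparison on two primary outcomes, which serves a stated study aim, can show a rise or a fall that reflects only window length. Second, T0 windows that vary between patients add variation to every contrast that uses T0, including the group-by-time contrast.

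**Working it through.** The documents give no event rate and no window length, so there is no figure of the plan to reproduce on this point. The sample-size calculation does not depend on it.

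**Inputs**
- Follow-up visits at 3, 6 and 9 months (Data Collection). The spacing is 3 months, or 365/4 ≈ 91 days. Treating 91 days as the follow-up window is an assumption.
- T0 look-back *w*: not stated. Assumed range 14 to 180 days.
- 36 participants per arm (Sample Size, before dropout allowance).
- Event rate, used only for illustration and simulation: 0.3 per day, assumed.

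**Step 1: expected shift with no true change.** With a constant rate *r*, the expected T0 count is *r* × *w* and the expected follow-up count is *r* × 91. The rate cancels in the ratio, which is 91/*w*.

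| T0 look-back (days) | Follow-up/T0 ratio |
|---|---|
| 14 | 91/14 = 6.5 |
| 30 | 91/30 = 3.03 |
| 60 | 91/60 = 1.52 |
| 91 | 91/91 = 1.00 |
| 120 | 91/120 = 0.76 |
| 180 | 91/180 = 0.51 |

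The shift is upward for a shorter T0 history, absent for an equal one and downward for a longer one.

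**Step 2: effect on the within-arm test.** A simulation drew Poisson counts with gamma-distributed patient rates (mean 0.3 per day, shape 1), 36 per arm, no true change, the same *w* for all patients, and 2,000 runs per setting. A one-sample t-test on the change from T0 to T1 in the experimental arm stood in for the GEE contrast. At the 5% level it rejected in 4.6% of runs for *w* = 91, and in 100% of runs for *w* = 14, 30, 60, 120 and 180.

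**Step 3: effect on the randomized comparison.** With no true change, the expected change in each arm is *r* × (91 − *w*). If *w* is alike in both arms, this term cancels in the difference between arms. In the same simulation the between-arm t-test on change rejected in 4.2% to 5.5% of runs over all settings, close to the nominal 5%.

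**Step 4: T0 windows that vary by patient.** Take two patients with the same unchanged rate of 0.3 per day and a 91-day follow-up window, so that each has an expected follow-up count of 0.3 × 91 = 27.3.
- With 14 days of T0 history, the expected T0 count is 4.2 and the expected change +23.1.
- With 90 days, the expected T0 count is 27.0 and the expected change +0.3.

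The gap of 22.8 events comes from the meters alone. Randomization balances such gaps between arms on average, so they appear as extra variance. How much power this costs depends on within-patient variability, which the documents do not give, so no figure is put on it here.

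**The case against.** **The follow-up window is not stated either.** The visit dates are fixed, but nothing says that the counts at T1, T2 and T3 each cover the three months since the last download. An equal look-back at all four visits fits the text just as well. This stands: the window is undefined at every visit, and the 91 days are an assumption.

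**The timing phrase may not define a window.** The App Use Data section uses the same phrase for a download from the backend, and the section on enactment of treatment skill speaks of downloads at each round. The phrase most naturally says when the download happens. This also stands. It should not be read as denying T0 any patient time, but then the article says nothing about how far back a count reaches.

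**The tempting stronger reading.** A reader might infer that the counts must rise from T0 to follow-up by construction. The documents do not support this. There is no shift if T0 covers about the same time as the later visits, and the shift reverses if the meter history is longer.

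**The randomized comparison survives.** This is correct under the null when windows are alike in both arms. The bias falls on the experimental-arm before/after contrast, which has no control group in any case.

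**A journal article may leave this to the full protocol.** This is fair as far as a missing look-back length goes, and the full protocol may give one. But the article does fix the metric, as a raw number per participant, together with detailed rules on who inspects readings and which reading counts. It then commits that metric to a before/after comparison. GEE does not exclude an offset, but none is named.

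**Conclusion.** The point holds as a defect of definition. Two of the listed primary outcomes are raw counts without an observation window or denominator at T0 or at T1 to T3, and they enter a planned before/after comparison. That comparison can be interpreted only if the time covered is the same at each visit or is allowed for in the analysis.

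If the follow-up counts cover about 91 days, a T0 history of 14 to 180 days moves the expected ratio from about 6.5 down to about 0.5 with no true change. These figures rest on the assumed windows and a constant event rate. The 100% rejection in the simulation also rests on the assumed 0.3 events per day and the assumed spread between patients.

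The primary randomized inference is not invalidated. There the cost is noise from T0 windows that vary by patient, of unknown size. The correction is worth making because it is cheap, and because the before/after comparison is a stated aim.

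**What to change.** In the Hyperglycemic Events and Hypoglycemic Events sections, define each outcome as the number of events in the same look-back window ending at each of T0, T1, T2 and T3, and state its length. Thirty days is one option. Any length up to the visit spacing keeps successive windows from overlapping. Apply the same window to diagnosed ketoacidosis and diagnosed hypoglycemia.

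Record for each visit the days of that window that the dated download actually covers. In the Statistical Analysis section, name a count model for these two outcomes in the GEE, with log(days covered) as the offset. A short T0 history is then handled by the offset and need not be discarded. The T0 count should be missing only when there are no dated readings.

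The cost is wording and analysis work, and the sample size does not change. The change can reach participants already enrolled if their dated downloads were kept. The downside is that follow-up readings outside the common window drop out of the before/after contrast. They can still serve a between-arm comparison over T1 to T3, with the same kind of offset. The offset corrects for time covered only. It does not correct for patients testing more or less often within that time.
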